### 9.2.3 Assessment of other Outcomes of Interest

- Adherence will be assessed at each study visit by questionnaire and pill count as described in section 8.4 for all patients. Adherence will also be assessed via a DTG + FTC plasma concentration at week 48 (performed retrospectively) for patient on an ARV regimen containing at least DTG + FTC.
- DTG and FTC drug plasma concentration levels will be determined by liquid chromatography coupled with tandem mass spectrometry (LC-MS/MS). This method is available at the Laboratory of clinical pharmacology at CHUV, Lausanne, Switzerland.
- DTG pharmacogenetic analysis will be performed at the Laboratory of clinical pharmacology at CHUV, Lausanne, Switzerland, only for patients included in the SHCS and who have signed a consent form for genetical analysis within the SHCS.
- Extra-visits outside scheduled study visits will be recorded in the electronic CRF by the study nurse or other (e.g. study coordinator, research associate) with the date and reason of consultation. Extra visits are all medical and non-medical visits reimbursed by the patient's health insurance.
- Study-related data, such as study drug distribution and return, randomization will be collected by the study nurse or other (e.g. study coordinator, research associate) as per protocol and recorded on study source documents and entered into the electronic CRF.
- Demographic data will be retrieved from the SHCS or the patient's medical file and will include: age, sex, ethnicity and level of education.
- HIV related data and medical history data will be retrieved from the SHCS or the patient's medical file and will include: date of HIV-1 infection (first documented positive HIV-1 serology), duration of viral suppression, nadir CD4 count, previous genotype, prior AIDS events (CDC C events), co-infection with hepatitis B or C, other ongoing medical conditions at baseline (i.e. diabetes mellitus, hypertension, etc.).

### 9.2.4 Assessment of Safety Outcomes

#### 9.2.4.1 Adverse Events

At every study visit starting from the randomization in the trial, i.e. from the baseline visit, we will record adverse event information (i.e. type of event, date of onset, duration, final outcome, action to be taken, assessment of severity, relationship with study drug(s) and/or procedure). For the definition and procedures, we are referring to section 10. CNS side effects will be recorded using a standardized questionnaire at week 2 (by phone call) and week 6 among patients new to DTG drug and reported as adverse events as well. Assessment of adverse events will be standardized in the CRF.

#### 9.2.4.2 Laboratory parameters

Efficacy laboratory such as HIV-1 RNA level will be quantified at every visit using PCR with a limit of detection of 20 copies/ml or less at the sites' virology laboratories. Plasma samples will also be collected at every visit, processed and stored at -80°C as per SHCS samples. In case of HIV-RNA measurement  $\geq 100$  copies/ml, stored plasma sample will be sent to the Laboratory of clinical pharmacology of the CHUV for DTG and FTC plasma concentration. In case of virological failure, stored plasma will be used for genotypic resistance testing. Otherwise, cells and plasma samples are stored at least until the publication of the final manuscript. Detailed instructions for sample collection, storage and shipment will be provided by the sponsor in the written standard operating procedure.

Safety laboratory (i.e. creatinine, CK, ASAT, ALAT, gamma-GT, alkaline phosphatases, glucose and lipid profile), full blood count and CD4/CD8 cell count will be measured at the local clinical chemistry, haematology and immunology/virology laboratories. Certificates and normal value ranges will be available at each study site in the investigator file. Laboratory abnormalities that are listed in the Adverse Event list should be graded accordingly (see details in the section 10).

#### 9.2.4.3 Vital signs

Blood pressure and heart rate will be measured after 10 minutes resting in a sitting position. Temperature will be collected and recorded in the CRF. Physical examination will include anthropometric measurements (weight and height), assessment of the cardiovascular, respiratory and gastrointestinal systems, as well as skin and central nervous systems as deemed necessary by the study physician.

#### 9.2.5 Assessments in participants who prematurely stop the study

Participants who prematurely stop the study will be asked to come in and complete the study procedures of the week 48 visit. Procedures are described in section 10.

### 9.3 Procedures at each visit

#### 9.3.1. Screening, visit 1 and informed consent (Week -4 to week-1) at SHCS center

Participants must give their written consent by signing the informed consent form prior to any study specific procedure. Results from a blood test performed before the screening visit is accepted for the Simpl'HIV trial if a patient is included in the SHCS and if the time window of -7 to -28 days to the baseline visit is respected. In such cases data should be entered in the database as part of the screening visit.

Screening visit can be done by the study nurse only (the presence of a medical doctor is not obligatory).

##### *Clinical assessments:*

- Demographics related data.

##### *Laboratory assessments:*

- HIV-1 RNA in the plasma;
- CD4 count;

- Full blood count;
- Safety serum chemistry: CK, creatinine, ASAT/ALAT, gamma-GT, alkaline phosphatases, glucose and lipid profile;
- Urinary  $\beta$ -HCG in women of childbearing potential.

Eligibility criteria will be checked by the study physician following the results of the screening visit. If some of the laboratory assessments are not done at the screening visit and this does not impact patient's eligibility, these assessments should be performed at baseline visit. In such cases the results will be entered in the database as part of the screening visit.

### **9.3.2. Baseline, visit 2 (Day 0) at SHCS center**

All assessments made at the screening visit must be reviewed and the eligibility criteria check-list completed by the study physician in order to randomise the patient. The randomisation will be performed by sending a completed electronic randomisation request from the study site in secuTrial. Details will be provided by the sponsor in the Standard Operating Procedure.

The randomisation confirmation will be filed in the study documents. The participant's assigned treatment groups and corresponding randomisation numbers will be recorded in the CRF.

#### *Clinical assessments:*

- Eligibility check;
- Questionnaires completion by the patient: visual analog scale, patient's monitoring satisfaction;
- Adherence check;
- Medical history including diagnosis, diseases and concomitant medications. Any ongoing conditions that could be recorded as adverse events during the course of the study should be recorded;
- Physical examination and vital signs;
- Start DTG+FTC dual maintenance therapy OR remain on standard cART;
- Start patient-centered monitoring OR remain on standard monitoring;
- Documentation of alternative option(s) chosen for patient-centered monitoring if randomised in patient-centered monitoring;
- Study drug distribution and documentation (DTG + FTC or standard cART).

#### *Laboratory assessments:*

- HIV-1 RNA in plasma. If the baseline visit is performed within 7 days from the HIV-RNA measurement used for the screening visit, it is not mandatory to repeat the HIV-RNA measurement at the baseline visit. In such cases, HIV-RNA result used for the screening visit will be entered as well for the baseline visit in the database.
- Sample plasma and cells sample storage. If a venipuncture is planned at the baseline visit only for storages and the patient is included into the SHCS, plasma and cell sample storage can be drawn at the screening visit.
- HIV-1 DNA from PBMCs by ddPCR (performed retrospectively)
- DTG-related pharmacogenetics host profile will be performed for all patients on DTG. This analysis will be performed retrospectively according to funding availability and only for patients included in the SHCS and who have signed a consent form for genetic studies.

### **9.3.3. Week 2 ( $\pm$ 3 days)**

#### *Clinical assessments:*

- CNS adverse event questionnaire for patients new to DTG (phone call with study nurse/physician for all subjects, regardless of the monitoring arm after randomisation).

### **9.3.4. Week 6 ( $\pm$ 7 days)**

#### *Clinical assessments:*

- Adherence check by the study nurse/physician (face-to-face visit or by phone call);
- Recording/update of concomitant medications (face-to-face visit or by phone call);
- Adverse events recording (face-to-face visit or by phone call);

- CNS adverse event questionnaire for patients new to DTG (face-to-face visit or by phone call);
- Study drug distribution (DTG + FTC or standard cART) at study center, chosen pharmacy or by mail depending of study arm and option(s) chosen by the patient.

*Laboratory assessments (at SHCS center or peripheral laboratory):*

- HIV-1 RNA in plasma;
- Plasma sample storage;
- Dolutegravir and emtricitabine plasma concentration if HIV-1 RNA measurement  $\geq 100$  copies/ml in plasma;
- Genotypic resistance test if 2 consecutive HIV-1 RNA measurements  $\geq 100$  copies/ml in plasma;
- Pharmacogenetic analyses if 2 consecutive HIV-1 RNA measurements  $\geq 100$  copies/ml in plasma only for patients included in the SHCS and who have signed a consent form for genetic studies;
- CK, ASAT/ALAT, gamma-GT and alkaline phosphatases if patient new to DTG drug;
- Glucose and creatinine if patient under DTG and metformine.

For patients randomised in the patient-centered monitoring arm, study drug distribution and laboratory assessments can be done before clinical assessments but within the time window of the visit.

### **9.3.5. Weeks 12 and 36 ( $\pm 7$ days)**

*Clinical assessments:*

- Adherence check by the study nurse/physician (face-to-face visit or by phone call);
- Recording/update of concomitant medications (face-to-face visit or by phone call);
- Adverse events recording (face-to-face visit or by phone call);
- Questionnaires completion: visual analog scale, PROQOL-HIV, (face-to-face visit or by phone call);
- Study drug distribution (DTG + FTC or standard cART) at study center, chosen pharmacy or by mail depending of study arm and option(s) chosen by the patient;
- Patient's monitoring satisfaction.

*Laboratory assessments (at SHCS center or peripheral laboratory):*

- HIV-1 RNA in plasma
- Plasma sample storage;
- Dolutegravir and emtricitabine plasma concentration if HIV-1 RNA measurement  $\geq 100$  copies/ml in plasma;
- Genotypic resistance test if 2 consecutive HIV-1 RNA measurements  $\geq 100$  copies/ml in plasma;
- Pharmacogenetic analyses if 2 consecutive HIV-1 RNA measurements  $\geq 100$  copies/ml in plasma only for patients included in the SHCS and who have signed a consent form for genetic studies;
- CD4 count, full blood count, safety serum chemistry (CK, creatinine, ASAT/ALAT, gamma-GT, alkaline phosphatases, glucose and lipids) if patient randomised in standard monitoring arm;
- Glucose, and creatinine if patient under DTG and metformine and patient-centered monitoring arm.

For patients randomised in the patient-centered monitoring arm, study drug distribution and laboratory assessments can be done before clinical assessments but within the time window of the visit.

### **9.3.6. Week 24 ( $\pm 7$ days) at SHCS center**

*Clinical assessments:*

- Adherence session by the study nurse;
- Recording/update of concomitant medications;
- Adverse event recording;
- Physical examination and vital signs;
- Study drug distribution and return (DTG + FTC or standard cART) according to site standard practice;
- Patient's monitoring satisfaction (possibility to change patient-centered monitoring options).

*Laboratory assessments:*

- HIV-1 RNA in plasma;
- Plasma sample storage;
- Dolutegravir and emtricitabine plasma concentration if HIV-1 RNA measurement  $\geq 100$  copies/ml in plasma
- Genotypic resistance test if 2 consecutive HIV-1 RNA measurements  $\geq 100$  copies/ml in plasma;
- Pharmacogenetic analyses if 2 consecutive HIV-1 RNA measurements  $\geq 100$  copies/ml in plasma only for patients included in the SHCS and who have signed a consent form for genetic studies;
- CD4 count, full blood count, safety serum chemistry (CK, creatinine, ASAT/ALAT, gamma-GT, alkaline phosphatases, glucose and lipids) if patient randomised in standard monitoring arm;
- Glucose, and creatinine if patient under DTG and metformine and patient-centered monitoring arm.
- Urinary  $\beta$ -HCG in women of childbearing potential.

**9.3.7. Week 48 ( $\pm 21$  days) or study discontinuation visit at SHCS center:**

*Clinical assessments:*

- Questionnaires completion: visual analog scale, PROQOL-HIV
- Adherence session by the study nurse;
- Recording/update of concomitant medications;
- Adverse event recording;
- Physical examination and vital signs;
- Study drug return (DTG + FTC or standard cART).
- Patient's monitoring satisfaction.

*Laboratory assessments:*

- HIV-1 RNA in plasma;
- CD4 count;
- Full blood count;
- safety serum chemistry: CK, creatinine, ASAT/ALAT, gamma-GT, alkaline phosphatases, glucose and lipid profile;
- Plasma and cells sample storage;
- HIV-1 DNA from PBMCs by ddPCR (performed retrospectively);
- Dolutegravir and emtricitabine plasma concentration for patients on ARV regimen containing at least DTG and FTC (performed retrospectively);
- Dolutegravir and emtricitabine plasma concentration if HIV-1 RNA measurement  $\geq 100$  copies/ml in plasma
- Genotypic resistance test if 2 consecutive HIV-1 RNA measurements  $\geq 100$  copies/ml in plasma;
- Pharmacogenetic analyses if 2 consecutive HIV-1 RNA measurements  $\geq 100$  copies/ml in plasma only for patients included in the SHCS and who have signed a consent form for genetic studies (performed retrospectively);
- Urinary  $\beta$ -HCG in women of childbearing potential.

*Costs assessments*

## 10. SAFETY

### 10.1 Drug studies

The Sponsor's SOPs provide more detail on safety reporting.

During the entire duration of the study, adverse events (AE) and serious adverse events (SAEs) are collected, fully investigated and documented in source documents and case report forms (CRF). Study duration encompassed the time from when the participant has been randomized in one study arm, i.e. starting from the baseline visit until the last protocol-specific procedure has been completed, including a safety follow-up period when needed.

#### 10.1.1. Definition and assessment of (Serious) Adverse Events and other safety related events

An **Adverse Event (AE)** is any untoward medical occurrence in a patient or a clinical investigation participant administered a pharmaceutical product and which does not necessarily have a causal relationship with the study procedure. An AE can therefore be any unfavourable and unintended sign (including an abnormal laboratory finding), symptom, or disease temporally associated with the use of a medicinal (investigational) product, whether or not related to the medicinal (investigational) product.

Adverse Events that need to be reported in this study are listed in the Adverse Event list (see Appendix 6). This list will be used starting from the baseline visit to confirming the absence or presence of any listed adverse event. Spontaneous, non-serious Adverse Events that are not listed in the Appendix 6 list will be collected in the patient's medical file according to local usual practice but will not be reported into the study-related document. Laboratory abnormalities listed in the Adverse Event list, will be reported as Adverse Events if they are at least a grade 3 and if they appear after randomization in the study (i.e. starting from the baseline visit). In case of laboratory abnormality already present before the randomisation, this will be considered as an adverse event only in case of worsening.

A **Serious Adverse Event (SAE)** is classified as any untoward medical occurrence that:

- results in death,
- is life-threatening,
- requires in-patient hospitalization or prolongation of existing hospitalisation,
- results in persistent or significant disability/incapacity,
- results in a congenital anomaly/birth defect, or
- is an important medical events that may not be immediately life-threatening or result in death, or require hospitalisation, but may jeopardise the patient or may require intervention to prevent one of the other outcomes listed above should also usually be considered serious. Examples of such events are intensive treatment in an emergency room or at home for allergic bronchospasm, blood dyscrasias or convulsions that do not result in hospitalisation, or development of drug dependency or drug abuse.

SAEs should be followed until resolution or stabilisation. See details in section 10.1.3.

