### 5.4 Safety Outcomes

1. Change in CD4 cell count from baseline to week 48;
2. Change in lipidic profile (total cholesterol, high density lipoprotein-cholesterol, triglycerides, low and high density lipoprotein-cholesterol) from baseline to week 48;
3. Change in glucose profile from baseline to week 48;
4. Change in Framingham-calculated cardiovascular risk from baseline to week 48;

5. Change in glomerular function rate from baseline to week 48;
6. Proportion of patients with an adverse event at week 48;
7. Proportion of patients with a serious adverse event at week 48;
8. Proportion of patients with a CNS adverse event throughout 48 weeks
9. Proportion of patients new to DTG with CNS symptom at 2 and 6 weeks after starting DTG;
10. Changes in patient weight from baseline to week 48.

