### 11.3 Statistical criteria of termination of trial

This is an open label study. The laboratory results that define treatment failure (HIV-RNA) of all participants included will be available within a week to the investigators. A detailed report including a summary of Serious Adverse Events, grade 3/4 Adverse Events, laboratory toxicities as well as virological failures, pregnancies and safety signals will be sent to the DSMB on a 6-monthly basis.

To protect the safety of the study participants, a safety interim analysis on the first 100 patients randomized will be done once reached the end of the time window for their 24 weeks study visit. The following data will be reviewed:

Safety data:

- Participant recruitment, accrual, retention and withdrawal information
- Adverse events (AEs) and serious adverse events (SAEs)
- Pregnancies
- Laboratory values
- Additional virological tests performed outside study schedule
- Any other safety-supporting data requested by the DSMB

Efficacy data:

- HIV-RNA data (primary endpoint measure)
- Genotype resistance test data (secondary endpoint)

We will also convene the DSMB in the following situations:

- (1) if > 2 patients experienced virological failure and a new resistances on DTG + FTC dual therapy before the planned interim safety analysis is done;
- (2) if new published or unpublished data show any major inconvenience of testing a DTG + FTC dual therapy arm.

The DSMB will then give recommendations regarding the continuation, modification or termination of the trial.

Stopping rules:

The DSMB may recommend stopping the trial for the following reasons:

- The data show a significantly increased risk of serious adverse events in one of the study groups;
- On the basis of a positive efficacy result only when the data are truly compelling and the risk of a false positive conclusion is acceptably low. The trial will only be stopped for positive efficacy if a strong statistically and clinically significant difference in virological success is seen between treatment arms;
- If interim data suggest that the simplified treatment/monitoring arm under study is of no benefit (trend indicating clear inferiority of the simplified treatment/monitoring arm), or that accrual rates are too low and/or that noncompliance is too great to provide adequate power for identifying the specified benefit, the DSMB may consider whether continuation of the study is futile and may recommend termination on this basis;

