##### *Clinical assessments:*

- ART changes since previous visit and reasons for changes;
- Current treatment satisfaction;
- Monitoring options changes since previous visit and reasons for changes;
- Current monitoring satisfaction;
- Number, date and value of HIV-RNA performed since previous visit;
- Number, date and results of genotypes resistance testing performed since previous visit\*;
- Grade 3 or 4 AE, SAE and pregnancy occurrence since previous visit (reported yearly);
- Quality of life questionnaire and visual analogues scale;
- Adherence questionnaire\*;
- Patient's weight and blood pressure\*.

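### The list-only reporting rule in section 10.1.1 has no exception for grade 3/4, drug-related or treatment-changing events, and does not match section 10.1, the adverse-event outcomes or the DSMB report

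*Protocol*

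**What the plan says.** Section 10.1.1 of the protocol first defines an adverse event broadly, as any untoward medical occurrence, related to treatment or not. It then narrows what is reported: "Adverse Events that need to be reported in this study are listed in the Adverse Event list (see Appendix 6"). For the rest, "Spontaneous, non-serious Adverse Events that are not listed in the Appendix 6 list" go to the local chart: they "will be collected in the patient's medical file according to local usual practice but will not be reported into the study-related document". The only grade threshold in that paragraph concerns laboratory abnormalities that are already on the list, which "will be reported as Adverse Events if they are at least a grade 3" and arise after randomisation.

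Section 10.1, immediately before, says that over the whole study AEs and serious AEs (SAEs) "are collected, fully investigated and documented in source documents and case report forms (CRF"). It does not mention a list.

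The data are used in these places:

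- Section 5.2 (outcome 10) and section 5.4 (outcome 6) count patients with any AE; the latter reads "Proportion of patients with an adverse event at week 48".
- Section 11.4.5 compares the proportion of drug-related events between the two treatment arms.
- Section 11.3 has the DSMB receive, every six months, "A detailed report including a summary of Serious Adverse Events, grade 3/4 Adverse Events, laboratory toxicities as well as virological failures".

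**The concern.** The collection rule is narrower than the outcomes and reports it feeds. A predefined list can be a sensible economy in a pragmatic phase IV trial of marketed drugs. Here, however, the exclusion depends only on whether the event is on the list and whether it is serious. It does not depend on how severe the event was, whether the investigator attributed it to the drug, or whether treatment changed because of it. Those are the three features that make an event matter for a safety comparison.

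Two things are at stake. First, sites have two conflicting instructions: section 10.1 tells them to put AEs in the CRF and section 10.1.1 tells them to leave some out. If sites resolve this differently, AE capture will vary between centres. Secondly, a reader of the results would take the proportion with an AE, the drug-related comparison and the DSMB's grade 3/4 summary at face value, when under 10.1.1 they would be limited to listed events plus SAEs. The trial aims to show that therapy can be simplified safely, with a combination that section 3.4 says no other study, to the authors' knowledge, is evaluating. Section 11.2 already concedes low power for adverse events.

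**Working it through.** No arithmetic applies. The protocol gives no rate of unlisted events, and Appendix 6 is named in section 19 but not shown. The check is to follow a hypothetical event through the text.

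**Case 1: a non-serious grade 3 clinical event, not on the list, judged possibly related to study drug.**

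| Place in protocol | What it calls for | What it gets if 10.1.1 is followed |
|---|---|---|
| 10.1 | AE documented in the CRF | Not entered: direct conflict |
| 9.2.4.1 | Type, severity, action taken and relationship recorded at every visit; refers to section 10 for procedures | Depends on which part of section 10 is applied |
| 5.2 (10), 5.4 (6) | Patients with an AE | Patient not counted on account of this event |
| 11.4.5 | Drug-related events by arm | Event absent |
| 11.3, six-monthly report | Grade 3/4 AEs to the DSMB | Event absent from that summary |

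**Case 2: a non-serious unlisted event after which the patient stops study drug.** Section 12.1.2 lists worksheets for a study drug discontinuation visit and a study discontinuation visit. Section 9.2.2 has a snapshot category for stopping because of an AE or death. Section 11.4.1 promises reasons for discontinuation where possible. The reason for stopping is therefore probably recorded. What 10.1.1 removes is the AE record itself: type, grade and causality. The patient could count as a discontinuation for an AE and still not count as having had one.

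**Case 3: an unlisted grade 1 or 2 event, unrelated, with no change of treatment.** It stays in the chart. This is the kind of event a list is meant to screen out, and little is lost.

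**What is captured whatever the list says.**

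- All SAEs go to the sponsor within 24 hours (10.1.2). The SAE definition in 10.1.1 includes important medical events that do not lead to hospital admission.
- Suspected new risks that call for safety measures go to the sponsor within 24 hours (10.1.2), and safety signals are part of the six-monthly DSMB report (11.3).
- CNS symptoms in patients new to dolutegravir are elicited by questionnaire at weeks 2 and 6 and reported as AEs (9.2.4.1).

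The gap is what remains: events that are unlisted, non-serious, not picked up by the CNS questionnaire and not escalated as a signal, yet are grade 3 or higher, drug-related or treatment-changing.

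**The case against.** The best case for the plan is that list-based collection is a disclosed choice, applied alike in every arm of a pragmatic phase IV trial of licensed products. Section 10.1.1 sets the operating rule, and the outcomes in sections 5.2, 5.4 and 11.4.5 can be read under it. An unexpected reaction of real consequence has other routes to the sponsor and the DSMB, and the DSMB may ask for further safety data at the interim. If Appendix 6 is long, or has a line for other grade 3/4 events, the practical gap may be close to nil.

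Much of this stands, and it rules out several stronger readings that a reader might infer:

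- *Such events never reach the study database.* Section 10.1 says the opposite of 10.1.1, so the supportable statement is that the two conflict.
- *Unexpected intolerance is invisible to the DSMB.* SAEs and safety signals reach it irrespective of the list.
- *Stops for unlisted AEs are lost, so the snapshot outcome is compromised.* The discontinuation worksheets and the snapshot category point the other way; only the AE detail goes missing.
- *AE rates before and after week 48 cannot be compared.* Section 13 does ask after week 48 for "Grade 3 or 4 AE, SAE and pregnancy occurrence since previous visit (reported yearly") with no reference to the list, but no planned analysis compares the two periods.
- *A number of lost events can be given by applying an unlisted share to the dolutegravir discontinuation rates in section 3.2.* Nothing in the protocol supplies such a share. Those rates also come from other populations, and section 3.7 treats patients new to dolutegravir as a subgroup, so not every patient assigned to dual therapy is new to it.
- *The omission favours the new regimen.* This is plausible, since section 6.1 has one arm switch and the other continue, but the documents do not show it.

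The objection leaves the mismatch in wording unanswered. Calling the list the operating rule does not explain why section 10.1 is unrestricted, why the outcomes and the DSMB report do not say *listed*, or why a severe or drug-related event is treated like a trivial one. The signal route also needs a site to suspect a new risk from the cases it sees; isolated events at separate centres may never be pooled.

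**Conclusion.** The concern holds as an internal contradiction with a practical consequence. Sections 10.1 and 10.1.1 give different instructions on recording AEs in the CRF. If 10.1.1 is followed, the AE proportions in sections 5.2 and 5.4, the drug-related comparison in section 11.4.5 and the DSMB's grade 3/4 summary in section 11.3 cover listed events and SAEs only, though none is worded that way. For an unlisted event that ends treatment, the reason is probably kept and the AE record is not.

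The size is unknown: it could be negligible or material, depending on how broad Appendix 6 is. The conclusion assumes that Appendix 6 does not itself contain a general entry for unlisted severe or drug-related events; if it does, the remaining task is to reconcile the wording. The primary virological comparison is not affected. This is an inexpensive improvement worth making, and it does not show that the trial cannot detect harm.

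**What to change.** Amend section 10.1.1 so that, in all arms, any AE, listed or not, is entered in the eCRF AE log if it is grade 3 or higher, is judged at least possibly related to study drug, or leads to a change or stop of any antiretroviral. Include these events in the six-monthly DSMB report and in the AE outcomes of sections 5.2 and 5.4, and make them available to the analysis in section 11.4.5. Unlisted, unrelated grade 1 or 2 events that do not affect treatment can stay in the chart. Reword section 10.1 to match. Label any analysis that remains list-only as *listed AEs and SAEs* wherever it appears.

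The AE log already exists (section 12.1.2) and AEs are already asked about at each visit, so the cost is a few extra log entries per site, with no added visits or tests. For patients who have already passed week 48, the log cannot be completed prospectively. For them the choice is retrieval from charts kept by local practice, which may be uneven across centres, or the restricted label.
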